### Participants

#### Sample size.

For fracture patients, we will enroll 265 participants who have sustained rotational ankle (specifically AO/OTA 44 types A-C [15]) fractures that are treated operatively. For control patients, we aim to enroll up to 40 healthy adults, who have never sustained a bone fracture. We will attempt to enroll the same percentage of males and females as the fracture patients.

The sample size was calculated based on the limited data from literature and our experiences on prior studies [16–18]. Dietz et al. reported that patients with fracture or trauma that developed complex regional pain syndrome (CRPS) had higher scores for pain, disability and all patient-reported outcomes than fracture controls [18]. Specifically, the effect sizes of the differences between these two groups were calculated as: Cohen’s d = .31 for neuropathic pain symptom inventory (NPSI), d = .34 for current pain, and odds ratio = 7.4 of developing allodynia. Hall et al. reported the percentage of Brief Pain Inventory (BPI – today’s pain) as 55%, 58% and 34% in the 1st, 2nd and 6th months, respectively, among 53 limb fracture patients [19]. In addition, Rbia et al. [7] and Friesgaard et al. [19] reported that about one in four ankle fracture patients would develop persistent neuropathic pain. Data on other outcomes are sparse. Based on the above information and assuming type one error of α = 0.05 and correlation between repeated measures as ρ = 0.6 and ratio for group size as 1:4, we estimated the total sample size needed to achieve sufficient power (β ≥ 0.8) were n = 205 for NPSI, n = 170 for current pain and for allodynia, and n = 213 for BPI. To maximize our ability to detect the differences, we chose the largest sample size n = 213. Our experiences following fracture patients longitudinally revealed 17% attrition rate (internal surveillance data for PREP-IT studies) [17,20]. We conservatively assumed the overall attrition rate to be 20%. Therefore, a total sample of N = 265 (expected to generate 53 BFNP patients) would need to be recruited.

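### The sample sizes for NPSI and current pain match a factor of 1 − ρ that suits a change contrast, but the quoted effect sizes are differences in level, for which 213 completers give roughly 44% to 66% power

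*Protocol article*

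**What the plan says.** All the inputs stand in the Sample size section of the protocol article.

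- Error rates: "assuming type one error of α = 0.05" and "sufficient power (β ≥ 0.8", the latter evidently meaning power of at least 0.80. Sidedness is not stated.
- Effect sizes, taken from a published comparison of trauma patients with CRPS and fracture controls: "d = .31 for neuropathic pain symptom inventory (NPSI" and "d = .34 for current pain". They are introduced with the words "the effect sizes of the differences between these two groups were calculated as", so they are differences in score between groups.
- Design assumptions: "correlation between repeated measures as ρ = 0.6 and ratio for group size as 1:4".
- Resulting totals: "n = 205 for NPSI, n = 170 for current pain and for allodynia, and n = 213 for BPI". The largest, 213, is adopted, and 20% attrition is added.
- Enrolment: "a total sample of N = 265 (expected to generate 53 BFNP patients". The same paragraph cites literature that about one in four ankle fracture patients develops persistent neuropathic pain.

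The section does not give the formula, the number of repeated measures or the contrast. The Data analysis section plans growth mixture models that test group differences in latent intercept and slope, both early after injury and over time. The legend to Fig 2 says that the study will focus on separating BFNP from No Pain, and it puts patients with other pain states in a group of their own.

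**The concern.** Repeated measures help a comparison of group levels only modestly when visits are positively correlated, because each further visit partly repeats what the earlier ones showed. With ρ = 0.6, the variance of a patient's mean cannot fall below 60% of the single-visit variance, however many visits there are. The stated sizes for NPSI and current pain imply a reduction to 40%. That is available for a change within patients, but the section gives no effect size for change.

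If the effect sizes are used as described, the section claims 80% power for differences that the design would detect about half to two thirds of the time. A non-significant result on these outcomes would then be given more weight than it deserves. The group sizes behind the calculation are also unclear, because the BFNP rate is not the same throughout the paragraph.

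**Working it through.** **Step 1. Independent-sample totals.** With two-sided α = 0.05, power 0.80 and ratio 1:k with k = 4:

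N = (1 + k)(1 + 1/k)(1.96 + 0.8416)² / d² = 6.25 × 7.849 / d²

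- d = 0.31: N = 510.5
- d = 0.34: N = 424.4

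**Step 2. Reproducing the stated sizes.**

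- 205 / 510.5 = 0.4016 and 170 / 424.4 = 0.4006
- 1 − ρ = 1 − 0.6 = 0.4
- 510.5 × 0.4 = 204.2, rounded up 205
- 424.4 × 0.4 = 169.7, rounded up 170

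Both stated figures are recovered. Among the factors tried at the stated 1:4 ratio and two-sided α, no group-mean or ANCOVA factor recovers both. A few variants come within 3% of the stated figures, but they need one-sided α or a different ratio.

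**Step 3. What the factor 0.4 stands for.** The mean of r later visits minus the mean of p earlier visits has variance factor (1 − ρ)(1/p + 1/r). With p = r = 2 this is 0.4 × 1 = 0.40. It is a change contrast and needs an effect size for change.

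**Step 4. Factor for a difference in level.** For the mean of m visits with exchangeable correlation, f = [1 + (m − 1)ρ]/m.

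- m = 4: (1 + 1.8)/4 = 0.70
- m = 3: (1 + 1.2)/3 = 0.733 (Table 3 schedules quantitative sensory testing at three visits)
- m = 1: 1.00
- limit for large m: 0.60

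**Step 5. Power at 213 completers, 1:4.** The groups are 42.6 and 170.4, so n₁n₂/(n₁ + n₂) = 34.08, with square root 5.838. Power = Φ(d/√f × 5.838 − 1.96). The detectable difference at 80% power is 2.8016 × √f / 5.838.

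| Contrast | f | Power, d = 0.31 | Power, d = 0.34 | Detectable d |
|---|---|---|---|---|
| Mean of 4 visits | 0.70 | 58% | 66% | 0.40 |
| Mean of 3 visits | 0.733 | 56% | 64% | 0.41 |
| Single visit | 1.00 | 44% | 51% | 0.48 |
| Factor implied by the plan | 0.40 | 82% | 88% | not applicable to a level |

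For 80% power with the mean of four visits, the totals are 510.5 × 0.70 = 357.3 (358 completers) and 424.4 × 0.70 = 297.1 (298 completers).

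**Step 6. The BFNP rate.**

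- One in four is 25%, a ratio of 1:3. A ratio of 1:4 is 20%.
- 265 × 0.8 = 212 completers. 25% of 212 = 53, and 20% of 265 enrolled = 53.
- At 1:4 among completers, 212 × 0.2 = 42.4 and 213 × 0.2 = 42.6, so about 42 to 43.
- If 25% is meant, the groups are 53 and 159. Then 53 × 159 / 212 = 39.75, with square root 6.305. With f = 0.70, power is 65% for d = 0.31 and 73% for d = 0.34.

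**The case against.** The strongest reply is that the section names no contrast, so the time-averaged mean is the reviewer's choice. The Data analysis section tests intercept and slope, and for change over time the within-patient error does scale with 1 − ρ. The design also offers a natural contrast with factor exactly 0.40. The section on measuring BFNP calls the 3–5 month and 6–9 month visits the chronic phase, which leaves two earlier visits to set against them. Adjusting for the first visit with three follow-ups does slightly better: (1 + 2 × 0.6)/3 − 0.36 = 0.373, which needs 190.6 and 158.4 patients and gives 84% and 90% power at 213.

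This stands as far as it goes. A reader might infer that 0.4 is simply a wrong formula. The documents do not support that, because the factor is valid for an identifiable contrast. What the reply does not supply is an effect size for that contrast. The values 0.31 and 0.34 are presented as group differences in score, and applying them unchanged to a change or adjusted score needs a justification that the section does not give. The first study visit also comes after surgery, so subtracting or adjusting for it would remove part of the early group difference that the Data analysis section sets out to test.

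Two further points limit the concern. The adopted 213 comes from BPI, not from these two outcomes. And 265 × 0.8 = 212 against a target of 213 is rounding, which should not be counted as an error.

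**Conclusion.** As written, the claim of at least 80% power for NPSI and current pain does not follow from the stated inputs. Read as differences in level, the effect sizes give power at 213 completers of 58% and 66% with four visits, 56% and 64% with three, and 44% and 51% with one.

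These figures rest on two-sided α, a normal approximation, exchangeable correlation of 0.6, the 1:4 ratio, and all non-BFNP fracture patients serving as comparators. The last assumption is generous. If patients with other pain states are left out, as the Fig 2 legend implies, the comparison group shrinks and power falls further. The documents give no share for that group, so the fall is not quantified.

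A reader might conclude that the whole study has 58% to 66% power instead of 80%. The documents do not support that. The BPI and allodynia sizes were not tested here, and a change or first-visit-adjusted contrast could reach 80% if an effect size for it were justified. The mismatch between one in four, 1:4 and 53 BFNP patients holds without any modelling assumption.

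**What to change.** Keep N = 265 and revise the Sample size paragraph as follows.

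1. State the contrast and the number of visits to which ρ = 0.6 applies.
2. For NPSI and current pain, replace 205, 170 and the claim of at least 80% power with the power from Step 5, or with a detectable difference at 1:4 of about 0.40 (four visits), 0.41 (three) or 0.48 (one). Alternatively, keep the factor 0.4, name the change contrast, and give and justify an effect size for it.
3. State whether the comparison group is all non-BFNP patients or No Pain only, and compute on that basis.
4. Use one BFNP rate throughout: either 25%, with ratio 1:3, 53 of 212 completers and four-visit power of 65% and 73%; or 20%, with ratio 1:4 and about 42 of 212 completers.

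The cost is one paragraph and, unless an effect size for change can be justified, a less favourable power statement for two outcomes. No additional patients or procedures are needed.

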#### Inclusion/exclusion criteria.

All fracture patients must meet all inclusion criteria and be absent of all exclusion criteria to be enrolled in the study. The criteria are listed in Table 1.

**Table 1 pone.0327605.t001:** Inclusion and exclusion criteria for fracture patients.

Inclusion criteria:
(1) 18–85 years of age
(2) Men and women
(3) Rotational ankle (specifically AO/OTA 44 types A-C) fracture that is treated operatively
(4) Abbreviated Injury Scale (AIS) less than 3 (i.e., classified as not a serious injury) for non-extremity body systems
(5) Able to speak, read, and understand English
Exclusion criteria:
(1) They are treated for a chronic pain condition prior to their qualifying injury
(2) They are on a pain contract
(3) Pathologic fracture
(4) Daily use of gabapentin or opioids prior to enrollment

All control patients must meet all inclusion criteria and be absent of all exclusion criteria that are listed in Table 2 to be enrolled in the study.

**Table 2 pone.0327605.t002:** Inclusion and exclusion criteria for controls.

Inclusion criteria:
(1) 18–85 years of age
(2) Men and women
(3) Able to speak, read, and understand English
Exclusion criteria:
(1) They have chronic pain or an ongoing acute pain condition
(2) They currently or have previously sustained a bone fracture
(3) Current Pain medication usage
(4) Any previous orthopaedic surgical procedures
(5) Must have been free of any surgeries for at least 5 years
(6) they have peripheral neuropathy
(7) they have a major surgery or a major disease or condition, as determined by the PI, such as cardiovascular disease, metabolic disease, renal disease, neurological disease, or serious psychiatric conditions.

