## Methods

### Study design and setting

This study will utilize a prospective cohort study design (Fig 2). We will enroll participants who have sustained rotational ankle (specifically AO/OTA 44 types A-C [15]) fractures that are treated operatively. Fracture patients will complete clinic assessment sessions at standard of care visits, including their first post-op appointment (2–4 weeks), at 5–9 weeks, at 3–5 months post-operatively, and at a 6–9 months follow-up visit. Clinic assessment sessions will include completion of questionnaires, blood draw, thermal imaging, quantitative sensory testing, and clinical assessment of infection, fracture healing, and radiographic arthritis. Questionnaires will be completed over the phone or in-person at each approximate time point. These visits will allow assessments during the subacute and chronic stages of BFNP. If fracture participants do not show for the in-person standard of care 6-month visit, the participant will be contacted by phone to collect patient reported outcomes (PROs). Along with this, at 1–1.5 years out the patient may be called for self-reported outcomes to assess if patients reporting chronic pain at 6–9 months still have persistent pain. A separate group of 40 uninjured healthy control participants will perform the same assessments during one study session. Enrollment procedures, including assessment of inclusion/exclusion criteria and informed consent, will occur in study session 1. This study was approved by the Indiana University (IU) Institutional Review Board. The study began January 1^st^, 2024 and will be completed on December 31^st^, 2028. We currently have 6 clinical subjects to date and expect to complete enrollment in June 2028. Data collection and results will be completed in 2029. No analysis has been implemented at this time.

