#### Recruitment.

**Fracture patients.** We will draw our case sample from patients undergoing surgery at IU Methodist Hospital with fractures of the ankle. We have a HIPAA waiver of consent for screening. IU Methodist Hospital Orthopedic research staff will review daily inpatient and outpatient OR schedules to screen for potentially eligible participants. We will be using the hospitals’ electronic medical records to obtain this information. Potentially eligible patients will be called on the phone by a member of the study team after their surgery but before their first post-operative appointment at the outpatient orthopaedic clinic. For those that express initial interest on the phone, study procedures, purpose, and inclusion/exclusion criteria will be reviewed. For those still interested, the patient will be given the following options:

1) provide verbal consent over the phone and then complete several patient-reported outcomes over the phone or online prior to the first in-person visit. A verbal script will be used when consenting subjects over the phone. Also, subjects who consent verbally will be sent the consent form via email to have during the phone call. Written consent is obtained during the first in-person visit.2) wait to provide any type of consent until the first in-person visit. In this case, all patient-reported outcomes are not completed until the in-person study visit after the written informed consent is obtained.

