### Procedures

See Table 3 for a list and timeline of study procedures for fracture patients. Our patient reported outcomes were chosen to align with the NIH HEAL Initiative (The Helping to End Addiction Long-term) common data elements [21].

**Table 3 pone.0327605.t003:** Calendar of study procedures for fracture patients.

	Daily	Standard of Care Follow-up			
		2-4** weeks	5-9** weeks	3-5** months	6-9** months
Screening	X				
Consent		X			
Inclusion/Exclusion criteria review^		X	X	X	X
Patient Characteristics form***		X			
Medical History form		X			
AIS form		X			
Injury Characteristics form****		X			
Clinical Follow-up form (fracture complications and healing) *****			X	X	X
Participant Follow-up form			X	X	X
Thermography		X	X	X	X *
Blood draw		X	X	X	X *
Quantitative sensory testing			X	X	X *
Immune cell analysis		X	X	X	X *
Chronic Pain Grading Scale				X	X
DNF – Interview				X	X
Ankle OA scale				X	X
Pain Map		X	X	X	X
Foot and Ankle Disability Index		X	X	X	X
Pain Catastrophizing Scale		X	X	X	X
PROMIS – Pain intensity		X	X	X	X
PROMIS – Pain Interference		X	X	X	X
PROMIS – Pain Behavior		X	X	X	X
PROMIS – Anxiety		X	X	X	X
PROMIS – Depression		X	X	X	X
PROMIS – Physical Function		X	X	X	X
PROMIS – Neuropathic Pain Quality		X	X	X	X
PROMIS – Sleep Disturbance		X	X	X	X

^Inclusion/Exclusion criteria review will occur prior to patient enrollment via a) medical record review to identify potential fracture participants and b) possibly over the phone. **All patient reported outcomes (PROs) may also be completed over the phone or online at each timepoint, if the patient prefers. *Only performed if session is in person vs. over phone. ***Age, gender, race, education level, socioeconomic status, workman’s compensation status. ****Open/Closed fracture classification, fracture description (both classic and AO/OTA classifications). *****Infection, nonunioun, post-traumatic arthritis, re-operation. At 1 to 1.5 years, we will review the patient’s medical record to assess for complications and we will contact by phone those determined to have BFNP to assess other PROs to see if their clinical pain state has resolved.

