#### Screening and enrollment visit for fracture patients (1^st^ visit, 2–3 weeks post-surgery).

The patient will complete the written informed consent document for the study at their 1^st^ post-operative standard of care visit with the first study visit completed in conjunction/right after the 1^st^ post-operative standard of care visit. At the first post-operative visit and over the phone (if applicable), study staff will review the informed consent and provide a clear explanation about what the study involves and its risks and benefits. Participants will be encouraged to take sufficient time to ask questions and to consider whether to volunteer to participate. We will also inform subjects about HIPAA regulations. Subjects will be asked to sign an Informed Consent Form to grant authorization for collection of health data. Those individuals who sign the forms will be enrolled in the study. Participant will be provided a written copy of the consent form. The remaining procedures of this visit are listed in Table 1 and further described below.

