#### Missing data.

There will be missing values related to dropout and nonresponse to surveys at different time points. If there is excessive or differential attrition across BFNP, BF no-chronic pain, and Healthy Control groups, we will identify baseline characteristics that differ between participants who did and did not have missing values. We will apply sensitivity analysis, such as inverse probability weighting methods, as needed [47]. If the procedure yields different results for the hypothesis tests, we will report study outcomes both with and without sensitivity analysis. Also, it is possible that participants may be found ineligible after study enrollment. Any data collected from these participants will not be included in the data analysis.

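### Exclusion 4 (daily gabapentin or opioid use) is dated to enrolment, 2–4 weeks after surgery, not to the injury, so read literally it selects on post-operative analgesic use

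*Protocol article*

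**What the plan says.** All references are to the protocol article.

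- **Exclusion 4** (Inclusion/exclusion criteria, Table 1): "4) Daily use of gabapentin or opioids prior to enrollment". It gives no look-back window, does not mention injury or surgery, and makes no exception for drugs prescribed around the operation.
- **Exclusion 1** (same table): "1) They are treated for a chronic pain condition prior to their qualifying injury".
- **Exclusion 2** (same table) concerns being on a pain contract and has no date.
- **Population**: inclusion criterion 3 requires a "fracture that is treated operatively", so everyone eligible has had surgery.
- **First contact** (Recruitment): the screening call takes place "after their surgery but before their first post-operative appointment at the outpatient orthopaedic clinic".
- **Enrolment** (Screening and enrollment visit): at the first post-operative visit, "Those individuals who sign the forms will be enrolled in the study". Study design and setting and Table 3 put that visit at 2–4 weeks; the heading of the enrolment section says 2–3 weeks.
- **Later review** (Table 3): the row "Inclusion/Exclusion criteria review" is marked at all four visits, while its footnote places the review before enrolment.
- **Late ineligibility** (Missing data): for participants found ineligible after enrolment, "Any data collected from these participants will not be included in the data analysis".

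**The concern.** Two criteria that both appear aimed at pre-existing pain problems carry different time references. Because enrolment follows the operation, the period before enrolment includes the injury, the surgery and the first post-operative weeks. Daily use of these drugs in that period may simply reflect how painful the fresh fracture is.

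The study wants early markers that separate later BFNP from No Pain (Fig 2 legend), says that mechanisms probably start soon after injury (Introduction), and trains its prediction models on data from 2–3 weeks after surgery (Supervised machine learning). Excluding people on a possible consequence of early pain would cut off part of the range of early predictors. It would also restrict the signature to operated patients not taking these drugs daily in the first weeks, although the machine-learning section asks for development data that resemble the real-world population. The inverse probability weighting offered under Missing data addresses dropout and nonresponse after enrolment; it cannot recover people who were never enrolled.

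**Working it through.** **Step 1. Time references side by side.**

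| Item | Dated to | Includes post-operative weeks? |
|---|---|---|
| Exclusion 1, chronic pain treatment | Qualifying injury | No |
| Exclusion 2, pain contract | No date | Not stated |
| Exclusion 4, daily gabapentin or opioids | Enrolment | Yes, as written |
| Enrolment | Signed consent, first post-operative visit | – |

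Taking verbal consent by phone as the reference date does not change this, because that call also follows surgery. Nor does the difference between 2–3 and 2–4 weeks, since both are post-operative.

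**Step 2. The planned yield.** Inputs from Sample size: 213 evaluable patients, 20% attrition, 265 recruited, 53 BFNP patients expected, and about one in four ankle fracture patients developing persistent neuropathic pain.

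- 213 / (1 − 0.20) = 266.25, rounded up to 267, against the stated 265. The difference is two patients and does not matter here; 265 × 0.80 = 212 completers.
- 212 × 0.25 = 53, as stated.
- The power calculation itself uses a 1:4 ratio: 213 / 5 = 42.6, about 43 BFNP patients.

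**Step 3. What selection could do to the yield.** Let e1 be the share of future BFNP patients excluded by criterion 4, and e0 the share of all others. With 25% BFNP before exclusion:

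BFNP share among those still eligible = 0.25(1 − e1) / [0.25(1 − e1) + 0.75(1 − e0)]

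The denominator is the share of the pool still eligible. The documents give neither e1 nor e0, so every row is an assumption.

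| e1 | e0 | Pool still eligible | BFNP share | BFNP of 212 |
|---|---|---|---|---|
| 10% | 10% | 90.0% | 25.0% | 53.0 |
| 50% | 50% | 50.0% | 25.0% | 53.0 |
| 20% | 10% | 87.5% | 22.9% | 48.5 |
| 30% | 10% | 85.0% | 20.6% | 43.6 |
| 40% | 20% | 75.0% | 20.0% | 42.4 |
| 50% | 20% | 72.5% | 17.2% | 36.6 |
| 60% | 30% | 62.5% | 16.0% | 33.9 |

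Example, 50%/20%: 0.25 × 0.50 = 0.125; 0.75 × 0.80 = 0.600; 0.125 / 0.725 = 0.172; 212 × 0.1724 = 36.6.

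The yield falls below 53 only when e1 exceeds e0. With equal use it stays at 53, and only the pool of eligible patients shrinks. The first two unequal rows stay above the roughly 43 that the 1:4 ratio implies, 40%/20% is about level with it, and the last two fall below.

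**The case against.** The strongest reply is that this is loose wording. Exclusion 4 sits beside criteria on prior chronic pain treatment and pain contracts, so pre-existing daily use was probably meant and staff may already apply it that way. A look-back definition could also stand in the full protocol, which is not shown. This limits the point to the effect of the rule as written. It does not remove the mismatch: the published rule states a reference date, and that date differs from exclusion 1.

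A reader might infer more, and four stronger readings are not supported:

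- **That such patients are in fact being removed.** Nothing in the article shows how the criterion is applied.
- **That patients can be removed later because of the outcome**, for instance by entering a pain contract after the fracture and failing a repeat review. Table 1 is introduced as a set of conditions for being enrolled, the Table 3 footnote puts the review before enrolment, and the Missing data sentence most naturally means an entry failure discovered late. Exclusion 4 also cannot reach drug use that begins after enrolment. What remains is that the later marks in Table 3 disagree with their footnote.
- **That the BFNP yield will fall by a known amount.** The fall depends wholly on unequal use, for which no figure is given.
- **That the biomarker–BFNP association is biased.** Restricting entry on a variable fixed before the outcome narrows the population and the predictor range. It does not by itself bias the association among those eligible.

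**Conclusion.** The point holds as a defect in the wording of an eligibility rule. Exclusion 4 is dated to enrolment, enrolment follows surgery by 2–4 weeks, and exclusion 1 is dated to the injury. Followed literally, exclusion 4 selects on post-operative analgesic use, a possible consequence of early fracture pain. The firmer consequences are a narrower range of early predictors and a narrower population for the signature.

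The effect on yield is conditional: 53 with equal use, and about 48 down to 34 of 212 under the unequal shares tried. These figures rest on an assumed 25% baseline risk and assumed exclusion shares. No stated sample-size figure changes as a direct result. That early daily use marks a group at higher risk of BFNP is a plausible inference, not something the article reports.

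**What to change.** Reconcile the time reference of exclusion 4, and of the undated exclusion 2, with exclusion 1 and the enrolment date. The investigators need to say which they mean:

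- If pre-existing use is meant, date both criteria to the qualifying injury.
- If post-operative use is meant, say so, restate the target population as the restricted one, and restate the expected BFNP yield with the use rates assumed.

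Two smaller consistency changes belong with this. Align the eligibility-review marks after the first visit in Table 3 with the footnote, and state under Missing data that results are dropped only for failure of a criterion as it stood at entry.

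Post-injury analgesic use may be recorded and examined in a sensitivity analysis. It should not be adjusted for by default: if it is a consequence of early pain, adjustment could remove part of the signal being sought.

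The cost is a minor ethics amendment and a change to the screening form. The Status section reports 64 fracture patients enrolled by 31 May 2025, leaving 265 − 64 = 201 at that date, so a prompt change would cover most of the cohort. Anyone already turned away under the literal wording cannot be recovered by analysis.

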### Outcome measurements

#### Measurement of BFNP in fracture patients.

The Chronic Pain Grading Scale (CPGS) will be used to determine whether fracture patients have chronic pain in the chronic phase of injury (3–5 month visit and 6–9 month visit). Fracture patients who report persistent pain (non-zero score on the CPGS) at 3–5 months and 6–9 months will also complete the Douleur Neuropathique 4 (DN4) questionnaire at the 3–5 months and 6–9 month visits.

**Chronic Pain Grading Scale (CPGS).** The CPGS grades chronic pain as a function of pain intensity and pain-related disability reported by the participant for the last three months [22]. The subscale score characteristic pain intensity will be used to categorize participants into those with and without chronic pain [23]. This item is the sum of three questions (current pain, worst pain, average pain over last month), each scored on an 11-point Likert scale with responses ranging from 0–10 for a maximum of 30 points. The participant will be asked to report only on pain related to the site of fracture. Participants scoring 1–30 on the characteristic pain intensity score in the last month at the site of fracture will be classified as having chronic pain. Patients reporting no pain (0) at the site of fracture in the last month will be classified as having no chronic pain. This tool has been used to assess chronic pain following trauma [23–25]. Internal consistency is acceptable with Cronbach’s alpha ranging from 0.67 to 0.74 depending on chronic pain condition and Kappa coefficient from 0.79 to 0.86. The CPGS has also shown good concurrent and prognostic validity [22,26].

**Douleur neuropathique 4 (DN4).** The DN4 is a validated and reliable screening tool for neuropathic pain consisting of 7 items [27,28]. The items relate to pain quality (i.e., sensory and pain descriptors) and are based on interview with the patient. The items of the DN4 are scored based on a yes (1 point)/no (0 points) answer. This leads to a score range of 0–7. The cut-off value for the classification of neuropathic pain is a total score of >3 [28,29]. The DN4 has been used to identify neuropathic pain in ankle and wrist facture patients [7,19].

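### The BFNP label has no step that separates peripheral neuropathy present before the injury from new fracture-associated neuropathic pain, and fracture patients are not screened for it

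*Protocol article*

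**What the plan says.** **Eligibility (Inclusion/exclusion criteria).** The article presents Table 1 as the complete list for fracture patients: "All fracture patients must meet all inclusion criteria and be absent of all exclusion criteria to be enrolled in the study". It has four exclusions:

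1. "They are treated for a chronic pain condition prior to their qualifying injury"
2. being on a pain contract
3. pathologic fracture
4. "Daily use of gabapentin or opioids prior to enrollment"

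The age range is "18–85 years of age". None of the four names neuropathy, diabetes or neurological disease.

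Table 2, for controls, excludes people if "they have peripheral neuropathy" (item 6). It also excludes major conditions "such as cardiovascular disease, metabolic disease, renal disease, neurological disease, or serious psychiatric conditions" (item 7).

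**Case definition (Study design, Fig 2 legend; Measurement of BFNP in fracture patients).** A score of at least 1 out of 30 on the CPGS pain intensity items places a patient in the Pain cohort and leads to the DN4 interview. For the CPGS the article says: "The participant will be asked to report only on pain related to the site of fracture". The DN4 has seven yes/no items, and "The cut-off value for the classification of neuropathic pain is a total score of >3". The DN4 paragraph says nothing about site, side or onset. Table 3 schedules the DN4 only at 3–5 and 6–9 months.

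**Use of the label.** BFNP is the outcome class in the growth mixture models (Data analysis) and the class label in the prediction models (Supervised machine learning).

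**The concern.** The study is about neuropathic pain that follows a fracture. The label that stands for it tests whether the patient has ankle pain and whether symptoms have a neuropathic quality. It does not test whether the neuropathy came after the fracture. A patient with long-standing sensory symptoms in the feet and slight residual ankle pain can meet both conditions.

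Three things are at stake:

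- **The case group.** It would mix new fracture-associated pain with older disease.
- **The predictors.** Old neuropathy is present from the first visit. Its blood profile (first visit onward) and its absolute detection thresholds (QST from 5–9 weeks) could appear as an early signature of BFNP. Cross-validation would not reveal this, because the same labelling error is in every fold.
- **The control comparison.** Controls are screened free of neuropathy and metabolic disease. A difference between fracture patients and controls could partly reflect those conditions and not the fracture.

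**Working it through.** **1. The route to a BFNP label, followed as written**

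| Step | Rule in the article | Effect on prior neuropathy |
|---|---|---|
| Enrolment | Table 1, exclusions 1, 2 and 4 | Removes neuropathy treated as chronic pain, under a pain contract, or on daily gabapentin or opioids. Leaves neuropathy that is untreated, painless before injury, or managed otherwise. |
| Pain gate | Fracture-site CPGS intensity of at least 1 of 30 | Removes neuropathy without fracture-site pain. Minor residual pain passes. |
| DN4 | More than 3 of 7 | No stated onset condition, and no DN4 before 3–5 months to compare with. |
| Label | Pain cohort plus DN4 positive | No rule for prior neuropathy. |

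The gap survives all four steps, although the first two narrow it.

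**2. The plan's own figures (Sample size)**

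- Recruitment: 213 / 0.8 = 266.25, against a stated 265 (within 3%).
- Completers: 265 × 0.8 = 212.
- Expected BFNP: 212 × 0.25 = 53, as stated. (53 is also 20% of 265.)
- NPSI, d = 0.31, two-sided α = 0.05 (assumed), power 0.80, ratio 1:4, total multiplied by (1 − ρ) = 0.4: 5 × 1.25 × ((1.96 + 0.8416) / 0.31)² × 0.4 = 204.2, rounded up to 205, as stated. The (1 − ρ) factor is inferred because it reproduces the figure; the article does not give the formula.

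No stated figure is shown to be wrong. The point concerns the definition, not the arithmetic.

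**3. Illustrative size**

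Two assumptions are needed: prior neuropathy in 2–10% of completers, and half of these labelled BFNP. The only related figure in the article is neuropathic pain in about 1 in 10 adults over 30 (Introduction). That is a general-population figure for pain, before the Table 1 exclusions.

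- Low: 212 × 0.02 = 4.2; half = 2.1; 2.1 / (53 + 2.1) = 3.8%.
- High: 212 × 0.10 = 21.2; half = 10.6; 10.6 / (53 + 10.6) = 16.7%.

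The denominator is the enlarged group, because mislabelled patients are added to the expected 53.

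If a quarter of the patients with prior neuropathy have genuine fracture-related neuropathic pain (the plan's own rate), only three quarters of these labels are wrong:

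- Low: 0.75 × 2.12 = 1.6; 1.6 / 54.6 = 2.9%.
- High: 0.75 × 10.6 = 7.95; 7.95 / 60.95 = 13.0%.

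**4. What that could do to power**

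For a measure that old neuropathy leaves unchanged, a false-case share s shrinks the difference to d(1 − s). At n = 213 split 42.6 to 170.4, power = Φ(d(1 − s) / √(0.4 × (1/42.6 + 1/170.4)) − 1.96).

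| s | d(1 − s) | Power |
|---|---|---|
| 0 | 0.310 | 0.82 |
| 5% | 0.295 | 0.78 |
| 10% | 0.279 | 0.73 |
| 15% | 0.264 | 0.68 |

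For a measure that old neuropathy does shift, dilution is the wrong model. The risk there is a spurious or inflated difference, whose size the article does not allow one to estimate.

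**The case against.** The case on the other side is substantial, and much of it stands.

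- **The DN4 paragraph is silent, not permissive.** A reader might infer that the DN4 is deliberately left unrestricted by site. The article does not say so. Interviewer wording is commonly left to the full protocol or the case report form, and the interview is triggered by fracture-site pain, so the natural reading is that it describes that pain. This stands for site. It does not settle onset: old neuropathy may already involve the ankle, and no stated rule addresses when symptoms began.
- **Old neuropathy alone does not produce the label.** Correct: the CPGS gate requires fracture-site pain. But 1 point of 30 is a low gate.
- **Existing exclusions help.** Exclusions 1, 2 and 4 remove part of the established painful neuropathy. What remains is the untreated, painless or otherwise managed part.
- **Different criteria for controls are not an error.** A reader might take the mismatch between the tables as the defect. It is not. Healthy controls may be screened more strictly, and the stated focus is BFNP against No Pain within fracture patients.
- **The contralateral ankle is not simply spoiled.** A symmetric neuropathy tends to cancel in a side-to-side difference. Absolute thresholds and blood markers have no such protection.
- **Excluding these patients has a price.** The machine-learning section wants a development dataset that represents real-world patients, and prior neuropathy may itself be a genuine susceptibility factor.
- **Adjustment is already possible.** A Medical History form is collected and the covariate list is open-ended. But the article does not name neuropathy or diabetes, and covariate adjustment does not correct a label.

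**Conclusion.** The point holds in limited form, as a should-fix. As written, fracture patients with some kinds of prior neuropathy can enrol, and the BFNP rule does not separate their old disease from new fracture-associated pain. Under the assumptions above, 2–11 labels would be affected, about 4–17% of the enlarged BFNP group, or about 3–13% if a quarter of those patients have genuine fracture-related pain. The prevalence and the one-half labelling factor are both assumed, so these are illustrations and not estimates.

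A reader might infer that the case label is invalid, or that recruitment should not continue without a new exclusion criterion. The documents do not support that. The pain gate and the existing exclusions limit the problem, no stated figure is wrong, and the remedy lies in the label and the analysis.

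**What to change.** Keep eligibility as it is, and make four changes:

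1. Flag prior peripheral neuropathy and diabetes for every fracture patient, including those already enrolled, from the Medical History form. This assumes that the form, whose content is not shown, records them.
2. Keep patients with prior neuropathy out of the primary BFNP label, or report them as a separate stratum, with a sensitivity analysis that includes them. Define the stratum by the flag alone, so that flagged patients without pain are handled in the same way.
3. Add the flags as covariates in the growth mixture and machine-learning models.
4. State that DN4 items refer to the painful fracture site and to symptoms that began after the fracture. The CPGS already has the site instruction.

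The cost is small: no new data collection if the form holds the history, one interviewer instruction, and slightly fewer BFNP cases in the primary analysis. Timing favours acting now. At 31 May 2025, 64 fracture patients were enrolled and 25 had completed the 6–9 month visit, so up to 265 − 25 = 240, before attrition, could still have that DN4 under the clarified instruction. For interviews already done, the onset of symptoms will be harder to recover, and the history flag has to serve instead.
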